## Abstract

**Background:**

No definitive treatment methods of curative for knee osteoarthritis (KOA). The combined therapies that into account both the biochemical and biomechanical may provide potential opportunities for treat KOA, and previous studies have demonstrated that the platelet-rich plasma of intra-articular injection (IAI-PRP) and exercise treatments afford more benefits than do their corresponding monotherapies. The absence of a specific exercise plan and detailed explanation renders the aforementioned study results questionable. Furthermore, Tai Chi (TC) with moderate-intensity, whole body movements and good adherence may prove to be more effective for treating KOA. However, few studies examined the effectiveness and safety of combined IAI-PRP and TC for KOA.

**Methods:**

This study protocol will be a placebo-controlled, assessor-blinded randomized trial involving 12-week intervention and 1-year follow-up. The stratified randomization will be used to randomly assign the 212 participants to four groups: group A (placebo IAI); group B (PRP IAI); group C (TC and placebo IAI); group D (TC and PRP IAI). Injection will be performed once a week, three consecutive times as a course, after a week of rest to continue the next course, a total of 3 courses (12 week). Additionally, the TC interventions will be carried out 3 days per week for a total of 12 weeks. The primary outcome measures will include the efficacy (Western Ontario and McMaster Universities Osteoarthritis Index), acceptability and safety of these interventions. The secondary outcome measures will include physical function (Timed Up and Go test), walking function (Gait Analysis), inflammatory factor levels (e.g., Interleukin-1 β, interleukin-6, vascular endothelial growth factor), quality of life (36-Item Short Form Health Survey), volume of patellofemoral cartilage and effusion-synovitis (MRI). Two-way of variance with repeated measures will be applied to examine the main effects of the group and the time factor and group-time interaction effects for all outcome measures.

**Discussion:**

This trial will be first one to propose an integrated scheme combing IAI-PRP and TC for treatment of KOA, based on the consideration of the biochemical and biomechanical pathogenesis of KOA. These results of the study will provide evidence with high quality for integrated IAI-PRP and TC to treatment KOA.

*Trial Registration* Chinese Clinical Trial Registry ChiCTR2300067559. Registered on 11 January 2023.

## Background

Knee osteoarthritis (KOA) is a chronically orthopedic disease with cartilage degeneration and knee function limitations, which manifests as pain, swelling, stiffness and dysfunction, and severely restricts daily activities and mobility [1, 2]. The epidemiological study reported that the pooled global prevalence of KOA is 22.9% in people aged 40 and over [3]. More importantly, the incidence of KOA has continued to grow over the past few decades, in line with the global phenomenon of longevity and aging populations [4]. There is an important effort worldwide to establish therapeutic strategies to modify the natural history of KOA [2, 5]. However, no definitive methods of curative or reverse degeneration process for KOA, which meaning that treatment focuses on ways to treat patient symptoms and slow the progression of the degenerative process.

The challenge of treatment methods lies in the complexity and unclearly of pathological mechanisms involved in KOA [6]. Although the exact pathophysiology mechanism is still unclear, the biochemical and biomechanical are recognized as the key mechanism to the occurrence and development of KOA [7–9]. In aspect of biochemical, the inflammatory factors, abnormal chondrocyte apoptosis, and extracellular degradation are closely associated with the occurrence and development of KOA [10, 11]. In aspect of biomechanical, the atrophy of quadriceps femoris, lower-extremity malalignment, and abnormal stress distribution of the knee joint are associated with pain aggravation and cartilage loss progression [9, 12]. It should be emphasized that the biochemical mediated processes and biomechanical factors are coupled in the KOA development, which probably causing a vicious circle of cause and effect [7]. As a result, the concept of combined therapies has been proposed to treat KOA that take into account both the two aspects, an example commonly seen is the combination of intra-articular injection and exercise training [13].

Intra-articular injection (IAI) is commonly used as a conservative treatment for KOA, as it has the potential to induce regenerative changes in tissue structure and alleviate symptoms [5, 14–16]. Among of some injectants, the platelet-rich plasma (PRP) is the most promising alternative during the pain alleviation, restoration of the functional capacity and potential tissue repairment for KOA, due to this contains large amounts of growth factors and anti-inflammatory cytokines [6, 17]. Several previous studies have reported that the IAI-PRP and exercise treatments afford more benefits than do their corresponding monotherapies in patients with KOA [18, 19]. However, the absence of a specific exercise plan and detailed explanation renders the aforementioned study results questionable. Such as, Kaszynski et al. [18] and Paterson et al. [20] permitted patients with KOA to participate in weight-bearing and progressive physical activities within tolerable limits, but they did not provide a comprehensive and specific exercise plan with detailed explanations; while Raeissadat et al. [19] provided the description of multi-angle isometric strengthening exercises for the knee muscles, it is important to note that knee extensor strength is just one aspect influencing the progression of KOA. In contrast, whole body movements that involve lower limb motion chains, center of gravity transfer, and posture control may prove to be more effective for treating KOA. As a result, it is crucial to develop a comprehensive and reproducible clinical protocol to reassess the clinical benefits of combining IAI-PRP and exercise.

Tai Chi (TC), as a moderate-intensity exercise training, was recommended by American College of Rheumatology for KOA management [21–23]. A systematic review reported that TC was an effective and safety way for relieve pain, improve muscle strength, adjust lower-extremity alignment, increase joint stability, and balance control for the patients of KOA [22]. Furthermore, few patients have complained of the side-effects after receiving TC exercise [24]. However, few studies examined the effectiveness and safety of combined IAI-PRP and TC for KOA. Furthermore, the differences of efficacy between IAI-PRP and TC in the KOA treatment were not clarified in the previous study.

Therefore, the placebo-controlled, assessor-blinded randomized trial will be design in the present protocol, which will include group A (IAI-placebo), group B (IAI-PRP), group C (TC + IAI-placebo), and group D (TC + IAI-PRP). This protocol will allow to be achieve the study purpose as follows:

Aim 1: To examine the effectiveness and safety of combined IAI-PRP and TC for KOA treatment by comparing the group D vs B or C.

Aim 2: To compare the differences of efficacy between the IAI-PRP and TC in the KOA treatment by comparing the group B and C.

Aim 3: To provide high-quality evidence of PRP for KOA treatment by comparing the group B and A.

## Methods/Design

### Study design

This protocol will be a placebo-controlled, assessor-blinded randomized trial, which will be included 12-week intervention and 1-year follow-up. This protocol will be conducted in accordance with the Standard Protocol Items: Recommendations for Interventional Trials (SPIRIT) [25]. A total of 212 patients diagnosed with KOA will be randomly and equally assigned into the group A (IAI-placebo), group B (IAI-PRP), group C (TC + IAI-placebo), and group D (TC + IAI-PRP). A brief flowchart of the entire study is shown in Fig. 1, and the schedule of events is provided in Table 1. The study protocol was approved by the Ethics Committee of Shanghai Seventh People’s Hospital (2022-7th-HIRB-067) and registered in the Chinese Clinical Trial Registry (ChiCTR2300067559).

**Fig. 1 Fig1:**
[figure not shown]
A brief flowchart of the entire study. *IAI* intra-articular injection, *PRP* platelet-rich plasma, *TC* Tai Chi, *WOMAC* Western Ontario and McMaster Universities Osteoarthritis Index, *TUG* Timed Up and Go test, *ROM* Range of Motion, *IL-1 β* Interleukin-1 β,*** IL-6*** Interleukin-6, *VEGF* Vascular Endothelial Growth Factor,* TNF-α* Tumor Necrosis Factor α*;* SF-36 36-Item Short Form Health Survey, *MRI* Magnetic Resonance Image

**Table 1 Tab1:**
[figure not shown]
Schedule of enrollment, intervention and assessments.

“√” means things will be done. *WOMAC* Western Ontario and McMaster Universities Osteoarthritis Index, *TUG* Timed Up and Go test, *ROM* Range of Motion, *IL-1 β* Interleukin-1 β,*** IL-6*** Interleukin-6, *VEGF* Vascular Endothelial Growth Factor,*** TNF-α*** Tumor Necrosis Factor α,** SF-36** 36-Item Short Form Health Survey

### Sample size

The sample size will be determined based on the priori power analysis through G*Power software version 3.1.9.2 [26]. In the calculations, ANOVA repeated measures between factor will be chosen, effect size 0.25, alpha 0.05, power 0.80, number of groups 4, number of measures 5, and the sample size is calculated as 168. Taking into account a conservative anticipation of a 20% drop-out rate, the final sample size will therefore be 53 in each group, with a total of 212 subjects.

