### Statistical analysis

All statistical analyses will be performed with IBM SPSS (Version 22.0, Chicago, IL, USA) by statisticians who are blinded to the group allocation. The outcomes analyses will be performed on an intention-to-treat basis. For the missing data, several sensitivity analyses will be conducted to evaluate their effects on the results. The Shapiro–Wilk will be used to test the normal distribution of the continuous variables for demographic and outcome measures. Continuous variables will be described as mean ± SD for normal distributions or median for non-normal distributions, categorical variables will be described as frequency. The χ^2^ test or Fisher’s exact test will be used to examine the comparisons between the four groups for categorical variables. When the normality of data distribution is found, two-way of variance with repeated measures will be applied to examine the main effects of the group and the time factor and group-time interaction effects. A simple effect post hoc analysis will be conducted, when time-group interaction is significant. Additionally, if homogeneity is not found, a linear mixed model will be adjusted for gender and KL grade. To mitigate bias and potential confounding variables, the propensity score matching (PSM) method will be employed [50]. Significant level for all tests will be set at 0.05 for all statistical tests and corrected for multiple comparisons using the Bonferroni-adjusted method, and 95% confidence interval will be reported.

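### The 80% power is for a four-group omnibus test; it does not carry over to the Bonferroni-corrected pairwise contrasts that are the aims, and the correlation behind 168 is not reported

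*Protocol article*

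**What the plan says.** The Sample size section gives the G*Power procedure and its inputs: "ANOVA repeated measures between factor will be chosen, effect size 0.25, alpha 0.05, power 0.80, number of groups 4, number of measures 5". It reports that "the sample size is calculated as 168" and then inflates for attrition: "Taking into account a conservative anticipation of a 20% drop-out rate, the final sample size will therefore be 53 in each group", 212 in all. No correlation among the repeated measures is listed, and no WOMAC difference or SD is attached to the effect size.

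The aims at the end of the Background are all comparisons of two arms. Aim 1 examines the combination "by comparing the group D vs B or C", Aim 2 compares B with C, and Aim 3 compares B with A.

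The Statistical analysis section tests group, time and group-by-time effects. It then states: "A simple effect post hoc analysis will be conducted, when time-group interaction is significant". The 0.05 level is to be "corrected for multiple comparisons using the Bonferroni-adjusted method"; the number of comparisons is not given. The Outcome measures section makes T1, the first of the five visits, a baseline before intervention.

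**The concern.** Three different tests are in play: the one that was sized (group main effect, 3 df, uncorrected), the one that triggers the post hoc work (group-by-time interaction, 3 × 4 = 12 df) and the ones that answer the aims (corrected pairs). The stated power belongs to the first only. A reader will naturally take 80% as the chance of answering the aims, and may then read a non-significant D vs B, D vs C or B vs C as evidence of no benefit.

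The sized effect is also averaged over a visit at which randomised groups should not differ. Finally, the chosen G*Power procedure needs a correlation, so 168 cannot be checked from the inputs listed.

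**Working it through.** **Inputs from the protocol:** f = 0.25, alpha 0.05, power 0.80, k = 4 groups, m = 5 measures, N = 168 (42 per arm), 20% drop-out, equal allocation. **Assumed, because not stated:** the correlation ρ (scanned), equal correlation between all pairs of visits, the Bonferroni divisor (4 named contrasts or all 6 pairs), and the pattern of the four means.

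**1. Reproducing 168.** For the between-factor test, λ = N·f²·m / [1 + (m − 1)ρ], with 3 and N − 4 df and N in multiples of 4.

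- ρ = 0.5, N = 112: λ = 112 × 0.0625 × 5 / 3 = 11.67, power 0.81 (N = 108 gives 0.797). So 112 would suffice.
- ρ = 0.9, N = 168: λ = 52.5 / 4.6 = 11.41, power 0.81 (N = 164 gives 0.799).
- ρ = 0.5, N = 168: λ = 52.5 / 3 = 17.5, power 0.95.
- Required N by ρ: 140 at 0.7, 152 at 0.8, 160 at 0.85, 168 from 0.90 to 0.925, 172 at 0.95.

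Drop-out: 42 / 0.8 = 52.5, rounded up to 53; 53 × 4 = 212. This agrees with the protocol.

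**2. Effect of including baseline.** If f = 0.25 holds at the four post-baseline visits and is zero at baseline, the five-visit average is 0.25 × 4/5 = 0.20. At N = 168 and ρ = 0.9, λ = 168 × 0.04 × 5 / 4.6 = 7.30 and omnibus power falls from 0.81 to about 0.60. At ρ = 0.5 it is 0.80.

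**3. Power for a named contrast.** f = 0.25 fixes the spread of the four means, not any one difference. In single-visit SD units it implies:

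- equal additive effects (B and C midway between A and D): D−B = D−C = B−A = 0.25√2 = 0.35;
- two-versus-two split: 2 × 0.25 = 0.50;
- only D differs: 4 × 0.25/√3 = 0.58;
- one extreme pair, the other two arms midway: 0.25√8 = 0.71.

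The unadjusted five-visit mean has SD √[(1 + 4ρ)/5]: 0.959 at ρ = 0.9 and 0.775 at ρ = 0.5. The non-centrality is (d/SD) × √(42/2), on 164 df, with critical t of 2.53 (0.05/4) or 2.67 (0.05/6). For the additive case at ρ = 0.9 this is (0.354/0.959) × 4.583 = 1.69.

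| Pattern (d) | ρ = 0.9: over 4 / over 6 | ρ = 0.5: over 4 / over 6 |
|---|---|---|
| Additive (0.35) | 0.20 / 0.17 | 0.34 / 0.29 |
| Two vs two (0.50) | 0.45 / 0.39 | 0.67 / 0.61 |
| Only D differs (0.58) | 0.59 / 0.54 | 0.81 / 0.77 |
| Extreme pair (0.71) | 0.80 / 0.76 | 0.95 / 0.93 |

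Under the additive pattern the 0.71 SD pair is D vs A, which no aim names.

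**4. The same contrast with baseline adjustment.** Take 0.354 SD as a post-baseline difference. The residual variance of the four-visit mean is (1 + 3ρ)/4 − ρ²: 0.925 − 0.81 = 0.115 at ρ = 0.9, and 0.625 − 0.25 = 0.375 at ρ = 0.5. The non-centralities are 4.78 and 2.65, so power at 0.05/4 is about 0.99 and 0.55.

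**The case against.** Much can be said for the plan.

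- **The sample size is not miscalculated.** A reader might infer from the missing correlation that 168 is wrong or that the trial is too small. Neither follows: 168 reproduces at one value of ρ, and a lower ρ gives the omnibus test more than 80% power. A condensed article may simply have left the input out. This stands, and it makes that part a matter of reporting.
- **Low contrast power is not established in general.** The 0.17 to 0.20 comes from one assumed pattern, a high correlation and an analysis that makes no use of baseline. Other patterns reach 0.80, and adjustment at ρ = 0.9 takes the additive case to about 0.99. This also stands. The documents do not show that the trial has little chance of answering its aims. They show that the stated 80% says nothing about that chance.
- **The interaction test is not plainly an absolute gate.** The Statistical analysis section also tests the group main effect and does not forbid other pairwise comparisons. True, but simple effects after a significant interaction are the only follow-up it describes.
- **Aim 1 sets no success rule.** A reader might take the conjunction to mean that beating one monotherapy is enough. The text lists comparisons and defines no criterion, and comparing D with each of B and C is at least as natural a reading. The wording is loose, and no more can be claimed.
- **Bonferroni is valid.** Replacing it is a preference.

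The mismatch survives all of this. It does not depend on an unseen analysis plan, because the article itself states the sizing test, the aims and the post hoc rule.

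**Conclusion.** The concern holds as a mismatch between the powered test and the aims, with a reporting gap beside it. The 80% refers to a four-group effect at an uncorrected 0.05, diluted by a baseline visit. It does not apply to D vs B, D vs C, B vs C or B vs A at a corrected level.

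On the unadjusted five-visit mean with 42 completers per arm and f = 0.25, contrast power is about 0.17 to 0.80 at ρ = 0.9 and 0.29 to 0.95 at ρ = 0.5. These ranges rest on the assumed mean patterns, divisor and equal correlations; a baseline-adjusted analysis could do much better. If the effect exists only after baseline, even the omnibus figure drops to about 0.60 at the correlation that 168 implies. No change in the number of patients follows from this.

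**What to change.** Keep 212 and amend the text:

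1. Report the correlation used in the calculation and its basis.
2. Say that the 80% refers only to the omnibus group effect averaged over the five visits.
3. For each of the four named contrasts, give the power or the detectable WOMAC difference at its corrected alpha, as a range over ρ and plausible patterns, and state the Bonferroni divisor.
4. Test the four contrasts directly as planned, baseline-adjusted contrasts in the mixed model on post-baseline WOMAC, not conditional on the interaction test. Keep a multiplicity correction: Bonferroni is valid, Holm is optional.
5. Reword Aim 1 as D vs B and D vs C, so that a claim for the combination rests on both comparisons.

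The cost is text and a little analysis work. The power stated for the aims may turn out less favourable than 80%.

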### Participants

The participants must fulfill the KOA diagnosis criteria of the American College of Rheumatology, including MRI or CT radiography and current joint symptoms based on self-report [27]. The participants will be further screened according to the inclusion and exclusion criteria for those who meet the diagnostic criteria.

### Inclusion criteria

The inclusion criteria will be as follows: (1) meet the diagnostic criteria for KOA; (2) aged 50–75 years; (3) Kellgren–Lawrence (KL) grade I to III based on radiographic classification; (4) without the experience of TC; (5) volunteer to take part in the study and sign the informed consent form.

### Exclusion criteria

The exclusion criteria will be as follows: (1) have the history of trauma, ligament damage, fracture, or surgery on the knee within 12 months, causing pain or functional problems; (2) have severe cardiovascular disease, damage of liver and kidney function, immune deficiency, diabetes mellitus, and blood diseases; (3) have other acute or chronic disorders or psychiatric conditions that will affect physical or cognitive functions; (4) have received medication or relevant intra-articular injection within the last 3 months; (5) have involved in any study related to exercise program within the last 6 months.

### Recruitment and enrollment

Two hundred and twelve participants with KOA will be recruited from the Shanghai Seventh People’s Hospital and neighboring communities, through the ways of flyers, posters, recommended by rehabilitation therapist or neurologist, and WeChat official account. We will communicate with potential participants with participation intention by telephone for the first step of screening and asked them to self-report whether they met the inclusion criteria. For the subjects who passed the first step of telephone screening, he or she will be invited to face-to-face examination and evaluation, and to fully determine that the participants meet the inclusion criteria and not meet the exclusion criteria. In addition, we will inform the purpose, method and potential benefits of the present study to all participants, as well as the principle of voluntary participation. All patients who met the inclusion criteria and agreement to participate will be required to provide their written informed consent.

Recruitment will start from February 1, 2024, until when 212 participants are enrolled.

### Randomization, allocation concealment and blinding

The stratified randomization with gender and KL grade as factors will be used to randomly assign the eligible participants to four groups. First, the participants will be grouped by gender. Then, male and female will be grouped by KL grade. After grouping, there will be six subgroups: (1) male, KL = I; (2) male, KL = II; (3) male, KL = III; (4) female, KL = I; (5) female, KL = II; (6) female, KL = III. For any one subgroup, the participants will randomly divide into group A, B, C and D group, and all group A, B, C and D group are merged to form a new group A, B, C and D group. The randomization number lists will be generated by the random number generator of the SPSS software (Version 22.0; IBM Corp., NY, USA).

The allocation of participants will be hidden in opaque numbered and sequentially sealed envelopes, prepared by a researcher who did not participate in the recruitment and assignment of the groups. The corresponding envelopes will be opened to determine a patient’s group assignment once the participants enrolled have completed all baseline assessments. In addition, physiotherapists with same level, TC coaches and IAI operators also will be followed randomization and randomly assigned to any group.

Due to the visible nature of the exercise intervention, blinding of the study investigators and the participants for TC will be impossible [28]. To ensure blinding of the PRP and concealment of randomization, the independent laboratory pharmacist prepared a syringe with PRP and a syringe with placebo (isotonic saline: 0.9% sodium chloride) [29]. They covered study syringes with a specially manufactured thick plastic covering sheath to conceal the appearance of the study intervention. After the intra-articular injection, the syringe covered by the sheath (containing either the remnants of the PRP or saline) will be handed back to the independent research assistant, who disposed of the syringe in effort to maintain blinding of the study team. The success of blinding will be assessed by asking patients just after the injections what treatment they thought they had received. Furthermore, blinding will be applied to the outcome assessors and statisticians who conduct the final statistical analyses in this protocol to avoid potential detection bias. The outcome assessors will be responsible for data collection and analysis, and they will not be involved in the subject recruitment process.

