### Interventions

All participants will receive health education recommended by the guidelines of Osteoarthritis Research Society International (OARSI) [30]. On the basis of health education, the group A will receive the placebo intra-articular injection; the group B will receive the PRP intra-articular injection; the group C will receive TC and placebo intra-articular injection; the group D will receive TC and PRP intra-articular injection. During 12-week intervention, intra-articular injection of PRP and placebo will be performed under ultrasound guidance. The frequency and dose of intra-articular injection will be consistent between the placebo and PRP in the four groups. Injection will be performed once a week, three consecutive times as a course, after a week of rest to continue the next course, a total of 3 courses (12 week). Additionally, the TC interventions in the Group C and D will be carried out 3 days per week for a total of 12 weeks.

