### Tai Chi

The Tai Chi program is mainly based on a nine-form Yang-style, which is a brief and modified version of 64-form Yang-style [34, 35]. It can be easily learned and practiced without restrictions on time and space. More importantly, it is suitable for the patients with KOA, because some movement patterns with high knee joint load are modified by the Tai Chi master to accommodate KOA symptoms and help limit dropouts. The patients will participate in three 60-min Tai Chi sessions conducted weekly for 12 weeks. Each session includes: (1) warm up and review of Tai Chi principles and techniques, 10 min; (2) Tai Chi exercises, 40 min; (3) cool-down relaxation, 10 min. The teaching is carried out by a Tai Chi master who has over 10 years’ experience conducting Tai Chi exercise. Information about the principles and skillsets of each form of TC, and Video clips will be provided to each participant for home learning.

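### Assigning injection operators to groups would nest operator within arm and weaken the PRP blind; operators should work across all four groups

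*Protocol article*

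**What the plan says.** In the protocol article, the section on randomization, allocation concealment and blinding describes opening the envelopes that give each patient's group. It then adds that "physiotherapists with same level, TC coaches and IAI operators also will be followed randomization and randomly assigned to any group".

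The Interventions section gives each group one product: A gets saline and B gets PRP, while "the group C will receive TC and placebo intra-articular injection; the group D will receive TC and PRP intra-articular injection".

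The blind of the injections has its own stated basis. An independent pharmacist prepares the syringes ("the independent laboratory pharmacist prepared a syringe with PRP and a syringe with placebo"), a sheath hides the contents ("They covered study syringes with a specially manufactured thick plastic covering sheath to conceal the appearance of the study intervention"), and an independent assistant takes back and disposes of each syringe. The check on the blind is addressed to patients: "The success of blinding will be assessed by asking patients just after the injections what treatment they thought they had received".

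Under Statistical analysis, a repeated-measures analysis of variance is "applied to examine the main effects of the group and the time factor and group-time interaction effects". The fallback mixed model adjusts for gender and KL grade. Neither includes the operator.

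On teaching, the Tai Chi section says: "The teaching is carried out by a Tai Chi master who has over 10 years’ experience conducting Tai Chi exercise".

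**The concern.** Randomising patients balances patients. Randomising a handful of operators to arms does not balance operators; it ties each one to an arm. Whatever an operator brings (needle handling, how much fluid is withdrawn, rapport) then travels with the product that arm receives. B vs A, which serves Aim 3, and D vs C, which is part of Aim 1, would compare product plus operator. The other planned contrasts would carry the same nesting.

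The second issue is the blind. An operator tied to one arm gives the same product to every patient, so a single clue, such as resistance on the plunger or a slipped sheath, tells that operator what all later injections contain. The operator could then convey expectation to patients, whose own WOMAC ratings are the primary efficacy outcome. The planned check asks patients only, so unmasking of an operator could go unseen.

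**Working it through.** **Inputs from the article.** Four groups; 168 patients before and 212 after a 20% drop-out allowance; 53 per group; three courses of three injections; one injectate per group; no operator term in either model.

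**Inputs assumed.** The article gives neither the number of operators per arm (c) nor the operator intraclass correlation (ICC). I use c = 1, 2, 4 and ICC = 0.01, 0.02, 0.05.

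**Step 1: the group size.** 168/4 = 42; 42/0.8 = 52.5, rounded up to 53; 53 × 4 = 212. The article's drop-out step reproduces, and this point does not contest it.

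**Step 2: what the sentence implies.** It follows directly on patient allocation and says staff are also randomised. Patients each go to one of A to D, so the plain reading is that each operator does too. Because a group receives one injectate, such an operator gives only PRP or only saline.

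**Step 3: exposure of the blind.** 3 × 3 = 9 injections per patient and 53 × 9 = 477 per arm if all are given, every one the same product. With one operator per arm, a clue reveals whatever remains of the 477; with c operators, the remainder of about 477/c. If operators are crossed with arms, a clue reveals that injection and at most that patient's other injections.

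**Step 4: type I error if operators are nested and ignored.**

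Design effect: DE = 1 + (53/c − 1) × ICC.

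True two-sided error of a nominal 5% test: 2 × [1 − Φ(1.96/√DE)].

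Worked case, c = 1 and ICC = 0.05: DE = 1 + 52 × 0.05 = 3.60; 1.96/√3.60 = 1.033; error = 0.302. The effective size is 53/3.60 = 14.7 per arm.

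| Operators per arm | ICC 0.01: DE, error | ICC 0.02: DE, error | ICC 0.05: DE, error |
|---|---|---|---|
| 1 | 1.52, 0.112 | 2.04, 0.170 | 3.60, 0.302 |
| 2 | 1.25, 0.080 | 1.51, 0.111 | 2.28, 0.194 |
| 4 | 1.12, 0.064 | 1.25, 0.079 | 1.61, 0.123 |

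With 42 completers per arm, the ranges across the three ICCs are 0.099–0.262, 0.074–0.166 and 0.061–0.107 for one, two and four operators. These are normal approximations for a single test at 5%, before the planned Bonferroni correction.

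**Step 5: could the analysis repair it?** A pairwise test that allows for operators has 2(c − 1) degrees of freedom at operator level: 0 for one per arm, 2 for two, 6 for four. It is impossible in the first case and weak in the others.

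**Step 6: the coaches.** Only C and D receive Tai Chi, so a coach cannot be assigned to just any of the four groups. One section speaks of coaches in the plural and another of a single master. If one master teaches both C and D, no nesting arises between them. If coaches are divided between C and D, only the comparisons involving those groups are touched, and B vs A is not.

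**The case against.** The strongest reply is that the sentence is ambiguous. In awkward English it may mean that equally qualified staff are spread at random over all groups so that no arm gets hand-picked providers, which would reduce bias. This stands as a limit on certainty. A reader might infer that the article fixes one operator per arm, so that no analysis could ever recover the product effect. It does not: no staffing numbers are given, and that conclusion holds only for exactly one operator per arm.

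A reader might also infer that the PRP blind depends on the operators. The text does not support that. The pharmacist, the sheath and independent disposal carry the blind, assessors and statisticians are blinded too, and nothing says operators know the product. Fixed assignment weakens this arrangement; it does not undo it. Asking patients for their guess may pick up expectation that has reached them, but it does not test the operators.

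Technique is partly standardised by ultrasound guidance, a defined injection point, a set needle gauge and volume, and aspiration beforehand. That argues for a small ICC, which is why the assumed range starts at 0.01. Rapport and handling remain.

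Finally, rotas are operational detail that an article may leave out. But this point does not rest on an omission. The article states an assignment rule, and on its plain reading that rule introduces bias.

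**Conclusion.** The point holds in conditional form. Followed as plainly read, the rule nests operator within arm, leaves operator differences entangled with PRP versus saline when operators are few, and lets one clue unmask an operator's later injections. The type I error figures (about 11–30%, 8–19% and 6–12% for one, two and four operators per arm) rest on assumed staffing and an assumed ICC of 0.01 to 0.05. They illustrate what could happen and do not estimate what will. If operators already treat patients from all four groups, the inflation disappears and only the wording needs repair.

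A reader might infer that Tai Chi coaching is likewise confounded between C and D. The single master described in the Tai Chi section would remove that, so what is firm there is the mismatch between the two sections. The sentence needs rewriting on either reading, and before patients are treated, because nesting cannot be undone afterwards.

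**What to change.** Replace the staff sentence with wording such as: *Operators are not assigned to groups. Every operator injects patients from all four groups using coded sheathed syringes, and the operator is recorded on the CRF for each injection.* The present sentence also names physiotherapists, so extend the same rule to them.

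State that the same Tai Chi instructor or instructors teach groups C and D. Reconcile the plural coaches in the randomization section with the single master in the Tai Chi section, and with the fact that only C and D receive Tai Chi.

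The cost is protocol wording, a rota that schedules operators across groups, and one extra CRF field. The sample size does not change.
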